# Protocol of a prospective multicenter randomized controlled trial of robot-assisted stereotactic lesioning in the treatment of focal drug-resistant epilepsy

**DOI:** 10.1186/s13063-023-07334-9

**Published:** 2023-06-09

**Keywords:** Drug-resistant epilepsy, Robot-assisted stereotactic lesioning, Randomized controlled trial

## Abstract

**Background:**

This protocol describes the design of a multicenter randomized controlled trial of robot-assisted stereotactic lesioning versus epileptogenic foci resection. Typical causes of focal epilepsy include hippocampal sclerosis and focal cortical dysplasia. These patients usually present with drug resistance and require surgical treatment. Although epileptogenic foci resection is still the most commonly used treatment for such focal epilepsy, there is increasing evidence that epileptogenic focus resection may lead to neurological impairment. The treatment of epilepsy with a robot-assisted stereotactic lesioning mainly includes two new minimally invasive surgical methods: radiofrequency thermocoagulation (RF-TC) and laser interstitial thermal therapy (LITT). Seizure-free is less likely to be achieved by these two procedures, but neurologic preservation is better. In this study, we aimed to compare the safety and efficacy of RF-TC, LITT, and epileptogenic foci resection for focal drug-resistant epilepsy.

**Methods:**

This is a multicenter, three-arm, randomized controlled clinical trial. The study will include patients older than 3 years of age with epilepsy who have had medically refractory seizures for at least 2 years and are eligible for surgical treatment with an epileptogenic focus as determined by multidisciplinary evaluation prior to randomization. The primary outcome measure is seizure outcome (quantified by seizure remission rate) at 3-month, 6-month, and 1-year follow-up after treatment. Postoperative neurologic impairment, spectrum distribution change of video electroencephalogram, quality of life, and medical costs will also be assessed as secondary outcomes.

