### Outcomes

#### Primary outcome

The primary outcome is the participant’s seizure remission rate, which was defined by the following formula:$$\mathrm{Seizure\,remission\,rate}=\frac{\mathrm{Baseline\,seizure\,frequency}(\mathrm{per\,month}) -\mathrm{ Post}-\mathrm{op\,seizure\,frequency }(\mathrm{per\,month})}{\mathrm{Baseline\,seizure\,frequency}(\mathrm{per\,month})}\times 100\%$$

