#### Secondary outcomes

Engel classification at one-year follow-up after surgery.The proportion of participants with neurologic impairment after surgery, primarily determined by the change in NI.SHH scale score at each post-operative visit and neurological physical examination findings at each post-operative visit.Spectrum distribution and Epileptogenic Index change of video EEG at each post-operative visit.Participants’ quality of life after treatment. Evaluation will be performed at each post-operative visit by the Quality of Life in Epilepsy-89 scale (adults > 17 years) and the Quality of Life in Epilepsy-31 scale (children 4–16 years).Epilepsy-related medical costs at each post-operative visit.

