### Statistical analysis

Statistical analysis will be mainly performed by researchers from Sanbo Brain Hospital, Capital Medical University, using the SAS 9.3 (SAS Institute Inc., Cary, NC, USA) software. Take the test level *α* = 0.05. The Kolmogorov-Smirnov test will be used to test whether the variables will be normally distributed. Measurement data conforming to normal distribution will express as mean ± standard deviation (‾X ± s), and measurement data not conforming to normal distribution will be expressed as interquartile range *M* (Q25, Q75). The *t*-test will be used to compare the normal distribution of continuous variables. The rank sum test will be used to compare the continuous variables that do not conform to the normal distribution. The chi-square test will be used to compare the categorical data. Univariate and multivariate methods will be used to analyze the preoperative and operative factors associated with seizure-free. Analysis of the primary outcome will be by intention-to-treat.

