**Outcomes**							
Seizure remission rate					X	X	X
Engel classification							X
ASMs		X		X	X	X	X
Neurological function examination		X		X	X	X	X
Scalp EEG		X			X	*X	X
NISHH		X					X
WAIS-IV-C/WCIS-IV-C		X					X
WADS-IV-C/WCDS-IV-C		X					X
QOILE-89/QOILE-48		X					X
PET		*X					*X
MRI		X			X	*X	X
Operative information			X				X
Adverse events				X	X	X	X

*X*, required; **X*, optional; *LITT* Laser interstitial thermal therapy, *EEG* Electroencephalography, *RF-TC* Radiofrequency thermocoagulation, *ASM* Anti-seizure medications, *WAIS-IV-C* Chinese version of the Wechsler Adult Intelligence Scale-IV, *WCIS-IV-C* Chinese version of the Wechsler Children’s Intelligence Scale-IV, *WAIS-IV-C* Chinese version of the Wechsler Adult Development Scale-IV, *WCIS-IV-C* Chinese version of the Wechsler Children’s Development Scale-IV, *QOLIE-89* Quality of Life in Epilepsy-89, *QOLIE-48* Quality of Life in Epilepsy-48, *PET* positron emission tomography, *MRI* Magnetic resonance imaging

All related data will be collected and entered into an eCRF and study database. The investigators and clinical coordinators will be responsible for ensuring that the required data are collected and entered into the eCRF. The original information will be kept in paper medical records for data traceability purposes. The eCRF will be printed as a paper version and stored in a dedicated locked filing cabinet.

Only authorized researchers will be allowed to process the research data under computer password protection. The final data will be anonymized by completely removing any participant’s identifying information.

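### The seizure remission rate is primary at 3, 6 and 12 months with no decisive visit and no joint rule, so the document does not fix the error rate of the primary claim

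*Protocol article*

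**What the plan says.** The Abstract (Methods) of the protocol article lists three time points for the primary outcome and does not rank them: "The primary outcome measure is seizure outcome (quantified by seizure remission rate) at 3-month, 6-month, and 1-year follow-up after treatment".

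The other places where a decisive visit could be named do not name one:

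- **Primary outcome section.** The outcome is the "seizure remission rate, which was defined by the following formula", a percentage reduction from baseline in monthly seizure frequency. The postoperative frequency in the formula carries no date.
- **Table 1 (Data management).** The row "Seizure remission rate" has the same mark at 90, 180 and 365 days.
- **Statistical analysis section.** "Take the test level *α* = 0.05", with no sidedness and no division between visits. The tests named for continuous data compare groups once each, for example: "The rank sum test will be used to compare the continuous variables that do not conform to the normal distribution". The only sentence specific to the primary analysis concerns the analysis set: "Analysis of the primary outcome will be by intention-to-treat".
- **Sample size section.** The calculation refers to a one-sided 95% confidence interval and a 10% margin, but to no visit.

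By contrast, one secondary outcome is tied to a single time: "Engel classification at one-year follow-up after surgery".

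**The concern.** A primary outcome should lead to one conclusion, and its time point is part of its definition. Here three results qualify equally as primary. The remission rate could favour a conclusion at 3 months and not at 12, or the reverse, and the document would not say which one the trial stands on.

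Two things are at stake. If the investigators may put forward whichever visit is positive, the chance of a false claim exceeds the nominal 5%. If they must succeed at every visit, the trial has less power than any single-visit calculation would suggest. The document does not say which of these applies.

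**Working it through.** **Inputs from the document.** Three primary time points (Abstract); test level 0.05 (Statistical analysis); one-sided 95% interval for noninferiority (Sample size). Because sidedness differs between these sections, both versions are shown.

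**Inputs that are assumed.** The correlation ρ between the test statistics at different visits is not given. It is taken as equal for all pairs and varied from 0.5 to 0.95. The power per visit is not given either; 80% is used for illustration. The results do not depend on the planned total of 240.

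**Reference point.** With one decisive visit, the false-positive rate is 1 − 0.95 = 0.05, the document's stated level.

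**Rule A: a positive result at any one visit may be claimed.** The three statistics follow a multivariate normal distribution with mean 0 and correlation ρ. The false-positive rate is

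P(any) = 1 − P(|Z1| ≤ 1.96, |Z2| ≤ 1.96, |Z3| ≤ 1.96)

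and, one-sided, the same with Zi ≤ 1.645. For independent visits this is 1 − 0.95³ = 0.143. For correlated visits it was simulated with 4 million draws. The one-sided column assumes that the true difference lies exactly on the noninferiority margin at all three visits, which is the worst case.

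| ρ | Two-sided 0.05 | Ratio to 5% | One-sided 0.05 |
|---|---|---|---|
| 0.5 | 12.5% | 2.5 | 11.8% |
| 0.7 | 10.9% | 2.2 | 10.3% |
| 0.8 | 9.8% | 2.0 | 9.2% |
| 0.9 | 8.4% | 1.7 | 8.0% |
| 0.95 | 7.3% | 1.5 | 7.0% |

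**Rule B: all three visits must succeed.** The chance that all three are falsely positive (one-sided 0.05) is 0.5% at ρ = 0.5 and 2.5% at ρ = 0.9, so there is no inflation. The price is power. With 80% power at each visit (two-sided 0.05), each statistic has mean 1.960 + 0.842 = 2.802. The chance that all three are significant, and the chance that the three visits disagree, are:

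| ρ | All three significant | Visits disagree |
|---|---|---|
| 0.5 | 61% | 34% |
| 0.7 | 66% | 26% |
| 0.8 | 69% | 21% |
| 0.9 | 72% | 15% |

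As a check, independence gives 0.8³ = 0.512, and the simulation returns 0.513.

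**Reading the two tables together.** The same text allows a false-positive rate well above 5% or one well below it with reduced power. Even when there is a real effect, the visits would give mixed answers in roughly one trial in seven (ρ = 0.9) to one in three (ρ = 0.5).

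**The case against.** The strongest reply is that this is a journal article. Test order, adjustment and modelling are commonly left to a full protocol or analysis plan, neither of which is shown. The Statistical analysis section gives general rules for all variables; it does not say that the primary outcome is tested separately at each visit, or that one positive visit is enough. The abstract could describe a single outcome followed over three visits.

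Much of this is fair, and it limits what can be claimed. A reader might infer that the trial's false-positive rate has in fact doubled. The document does not support that: it states no any-visit rule and no correlation, the ratio is about 2 to 2.5 only for correlations of 0.8 down to 0.5, and an all-three rule removes the inflation altogether.

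A reader might also multiply the three visits by all pairwise comparisons of resection, RF-TC and LITT and quote the error rate for nine tests. That is not supported either. The Randomization and blinding section allocates 1:1 to lesioning or resection and calls RF-TC and LITT subgroups, and no section declares nine confirmatory tests. Which arms are compared is a separate question.

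What the reply does not answer is the time point itself. It belongs to the definition of the primary outcome, and the article is not silent on it: it states three. An unseen analysis plan that chose one would be changing the declared primary outcome. The single-outcome reading would still need a statement of which visit, or what summary over visits, decides.

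**Conclusion.** The point holds as an ambiguity in the primary outcome, not as a demonstrated inflation. Three time points are declared primary at one level of 0.05, with no decisive visit and no joint rule, so the document does not fix the error rate of the primary claim.

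The size depends on a rule that the document omits. Under an any-visit rule the false-positive rate is about 8% to 12.5% two-sided, or 8% to 12% one-sided with the true difference on the margin, for correlations of 0.9 to 0.5; it is about 7% at 0.95. Under an all-three rule the error rate stays below 5%, but 80% power per visit becomes about 61% to 72% for correlations of 0.5 to 0.9. Correlation and per-visit power are assumptions. The sponsor should correct this; it does not invalidate the design.

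**What to change.** Name one decisive time point for the primary outcome, in the same words, in the Abstract, the Primary outcome section and the Statistical analysis section. Twelve months is the natural choice, because it is the last visit and the time of the Engel assessment. List 3 and 6 months as secondary, reported with confidence intervals and without a confirmatory claim.

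If the sponsor prefers to keep all three as primary, either of these also settles the matter, provided that it is written down:

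- an adjusted level, for example 0.05 / 3 = 0.0167 per visit, which holds the total at no more than 5%;
- a requirement to succeed at all three visits, with the power recalculated for that rule.

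The text is short, but the step is more than editorial. The Trial status section dates the first recruitment to 20 September 2022. Under Ethics and communication, modifications go to the ethics committee, and important ones need health commission approval before they take effect. The registry entry may also need updating. The choice should be made before those deciding have seen outcomes by arm. With 12 months as the decisive visit, the sponsor gives up an early primary claim. All visits and data are kept.

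The comparison of arms for the primary analysis should be settled separately.

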**Trial registration:**

Chinese Clinical Trials Registry ChiCTR2200060974. Registered on June 14, 2022. The status of the trial is recruiting, and the estimated study completion date is December 31, 2024.

## Background

Epilepsy is a common disease of the nervous system causedby different causes, with spontaneous, recurrent, and unpredictable seizures as the main characteristics. It also has numerous neurobiological, cognitive, and psychosocial consequences [1]. Several epidemiological studies show that the incidence of epilepsy is 5.5–7.3‰ [2–4]. Drug therapy is the preferred treatment for epilepsy at present. However, about 30% of patients are still unable to control their seizures after continuous treatment with two or more appropriate anti-seizure medications (ASMs), which are defined as drug-resistant epilepsy (DRE) [5, 6]. In cases of drug failure, optimal seizure control usually requires neurosurgical intervention targeting the epileptic foci. Epilepsy surgery can be divided into diagnostic surgery (subdural electrode implantation, stereotactic multicontact electrode implantation, etc.), resective surgery (lesion resection, lobectomy, hemispherectomy, etc.), and palliative neuromodulation surgery (vagus nerve stimulation, deep brain stimulation, etc.) [7–9]. Patients with drug-resistant focal epilepsy can benefit from the removal or disconnection of a circumscribed brain region to achieve complete seizure control or at least reduce disabling seizures. Among carefully selected patients, the proportion of individuals who are seizure-free after surgery ranges from 50 to 80% [10, 11].

In the 1960s, Talairach and Bancaud innovatively took the anterior and posterior connections of the brain as the benchmark for homogenization, which created the stereotactic surgery technique in neurosurgery [12]. In recent years, with the rapid development of robot-assisted technology, the stability, accuracy, and economy of stereotactic surgery have made great progress. With the assistance of a robot, the implantation time of multicontact electrodes has been shortened to 3–5 min per electrode, and the accuracy of entry point, angle, and other parameters has been significantly improved; thus, the safety of surgery has been improved [13, 14]. Today, stereoelectroencephalography (SEEG) provides a unique approach to exploring the pathophysiology of epilepsy and pinpointing the epileptogenic network that no other noninvasive examination can provide. At the same time, because of the advantages of nerve function protection, stereotactic lesioning accounts for an increasing proportion of surgical treatment in major epilepsy medical centers around the world.

In the field of epilepsy surgery, stereotactic lesioning mainly includes two forms, one is SEEG-guided radiofrequency thermocoagulation(RF-TC) and the other is laser interstitial thermal therapy (LITT). RF-TC has been used for a long time, and it has been applied to several nervous system diseases such as epilepsy and trigeminal neuralgia [15]. Its application in the field of epilepsy is mainly achieved under the guidance of SEEG electrode implantation. Its effectiveness has been reported in large cohorts from several centers in Marseille, Lyon, Milan, and other European centers [16, 17]. Zhao et al. demonstrated its effectiveness in the treatment of mesial temporal lobe epilepsy by SEEG-guided RF-TC [18].

LITT is a kind of thermocoagulation surgery which is guided by magnetic resonance or stereo-electroencephalography and monitors the temperature and range of heat generated by laser in real time. It has a wide range of applications and can be used to treat a variety of diseases, including intracranial tumors and epilepsy. Curry et al. first used LITT to treat children with DRE and achieved some efficacy [19]. Since then, several clinical studies with relatively small sample sizes have reported the success of this technique in the treatment of medial temporal lobe epilepsy, hypothalamic hamartoma, periventricular nodular heterotopia, and focal cortical dysplasia [20–23].

Due to some limitations of existing studies, there is not enough evidence to prove the effectiveness of stereotactic lesioning of focal drug-resistant epilepsy. In China, there is no guideline for stereotactic lesioning in the treatment of focal drug-resistant epilepsy. In this study, we aimed to evaluate the efficacy and safety of stereotactic lesioning compared with resective surgery.

## Methods/design

### General study design

A multicenter, randomized controlled, parallel-group clinical trial will be conducted at Sanbo Brain Hospital, Beijing Tiantan Hospital, and Xuanwu Hospital. This study has been registered in the Chinese Clinical Trial Registry before the enrollment of participants (http://www.chictr.org.cn, registration number: ChiCTR2200060974).

Participant baseline information will be collected approximately 10 days before surgery, including participant demographics, seizure status, use of ASMs, neurological status, electroencephalogram (EEG), and magnetic resonance imaging (MRI) findings. The perioperative information of the participants will be recorded based on the surgical records and anesthesia records, including length of operation, amount of bleeding, complications, and cost of operation. The participants will be followed up for three times at 3, 6, and 12 months after the operation. The timeline of this study is shown in Fig. 1. The baseline information mainly includes the following:Seizure condition: seizure frequency (time/month), seizure duration, severity, etc.Neurological impairment: neurological function physical examination and National Institutes of Health Stroke Scale (NIHSS) score.Use of anti-seizure medications: type and dosage of drugs.Preoperative EEG examination: scalp EEG spectrum distribution, EEG Epileptogenic Index, etc.Preoperative MRI.Quality of life: using the Quality of Life in Epilepsy-89 scale for adults (ages 17–60) and the Quality of Life in Epilepsy-48 scale for children (ages 14–16). Patients not in the above age range will not be assessed for quality of life.Cognitive function: using the Chinese version of the Wechsler Intelligence Scale-IV and the Chinese version of the Wechsler Development Scale-IV.

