### Randomization and blinding

Randomization will be performed by independent investigators with the SAS (9.3, SAS Institute Inc., Cary, NC, USA) software. The resulting list of random numbers has been placed into sequentially numbered, sealed, opaque envelopes. Based on the information obtained from the envelopes, consecutively enrolled participants will be randomly assigned, in a 1:1 ratio, to stereotactic lesioning or classical epileptogenic zone resective surgery. Patients who are assigned to stereotactic lesioning surgery will be also assigned in a 4:1 ratio to a subgroup of RF-TC and a subgroup of LITT. The same group of neurosurgeons at different centers (three groups in total) will be responsible for different procedures for each participant.

Researchers and clinical research coordinators participate in the grouping process. Clinical research coordinators are responsible for informing patients, but they are not involved in the patient assessment and treatment process. All subjects and clinicians will be aware of the trial group assignments before surgical treatment, outcome assessors. However, outcome assessors and statisticians will not be aware of the subgroups of subjects

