### Data management

All baseline information and outcome-related data will be evaluated and collected by two experienced clinicians (one neurologist and one neurosurgeon). Detailed data collection and follow-up time are shown in Table 1. Each patient’s data will be completed into an electronic case report form (eCRF) by an independent clinical research coordinator. Participants will be given trial information to improve participation. In order to ensure the completion of the follow-up, we will contact participants by phone in advance.

**Table 1 Tab1:** Participant timeline

**Study period**	**Enrollment**	**Allocation**	**Operation**	**Follow-up**	**Follow-up**	**Follow-up**	**Follow-up**
**Time point**	− 10 days	− 7 days	0	7 ± 2 days	90 ± 7 days	180 ± 14 days	365 ± 14 days

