**Participants**							
Eligibility screen	X						
Informed consent	X						
Randomization	X						
Demography		X					

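### Table 1 does not secure baseline measurement before the arm is known, and the text does not secure assessor blinding to lesioning versus resection

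*Protocol article*

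**What the plan says.** **Timing, in the text.** General study design in the protocol article states: "Participant baseline information will be collected approximately 10 days before surgery, including participant demographics, seizure status, use of ASMs". Its list of baseline items begins with "Seizure condition: seizure frequency (time/month), seizure duration, severity, etc".

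**Timing, in Table 1 (Data management).** The first column is Enrollment at day -10 and the second is Allocation at day -7. The row "Randomization" is marked under Enrollment. Demography, ASMs, neurological examination, scalp EEG, the stroke scale (NIHSS), the Wechsler scales, quality of life and MRI have their pre-operative mark under Allocation. The only seizure-frequency entry is the remission rate, marked at days 90, 180 and 365.

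**Primary outcome.** The Primary outcome section defines the remission rate as baseline minus post-operative monthly frequency, divided by baseline monthly frequency.

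**Who knows the arm.** Randomization and blinding says: "All subjects and clinicians will be aware of the trial group assignments before surgical treatment". That sentence then ends in a stray mention of outcome assessors. The next one says "outcome assessors and statisticians will not be aware of the subgroups of subjects". Earlier in the same section, *subgroup* is the term for RF-TC versus LITT within the lesioning arm.

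**Who evaluates.** Data management says: "All baseline information and outcome-related data will be evaluated and collected by two experienced clinicians (one neurologist and one neurosurgeon".

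**The concern.** In an open trial, a baseline protects the comparison only if it is recorded before anyone can know the arm. Followed literally, Table 1 takes the stroke-scale, EEG and quality-of-life baselines about three days after randomisation. These are the reference points for secondary outcomes. For the primary outcome, the baseline count is the denominator of every patient's result, and the table gives it no visit at all. If the count were recorded or revised with the arm known, the remission rate could shift without any change in seizures.

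The follow-up side has a related weakness. Post-operative seizure frequency enters the numerator. If the people scoring it know whether the patient had lesioning or resection, the main comparison is open to assessment bias, whatever they know about RF-TC versus LITT. Baseline values collected after disclosure cannot be repaired at analysis, so the order has to be fixed in the protocol.

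**Working it through.** The article gives no figure to reproduce on this point. The check sets its statements side by side and then uses the primary-outcome formula for an illustration.

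**1. Order of randomisation and baseline**

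| Item | General study design | Table 1 |
|---|---|---|
| Randomisation | not dated there | day -10 (Enrollment) |
| Demography, ASMs, neurological status, EEG, MRI and the other listed measures | about day -10 | day -7 (Allocation) |
| Baseline seizure frequency | about day -10 | no row |

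The two sources disagree on the date of the listed measures. On Table 1's dates, randomisation comes 10 - 7 = 3 days before them. If the randomisation mark is misplaced and belongs under Allocation, randomisation and baseline share one column and the order within that visit is unstated. If the text is right and the table is wrong about baseline, both fall at about day -10, again with no stated order. No reading places baseline clearly first.

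**2. The primary-outcome denominator**

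Only General study design dates the seizure count, at about day -10. The eligibility screen, also at Enrollment, needs at least one disabling seizure per month. That requires someone to judge frequency, but it is a threshold and not the recorded count used in the formula.

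**3. Blinding**

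- All clinicians know the assignment before surgery (Randomization and blinding).
- Two clinicians evaluate all baseline and outcome data (Data management).
- Together, these imply evaluators who know lesioning versus resection.
- The blinding statement names outcome assessors but limits what is hidden to the subgroups, which in that section means RF-TC versus LITT.
- The article does not say whether the outcome assessors and the two clinicians are the same people.

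**4. Illustration of sensitivity**

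Let R be the true remission rate and b the fraction by which baseline frequency is over-recorded in one arm. Neither value is in the article; both are assumed.

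Apparent remission = 1 - (1 - R)/(1 + b)

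- R = 50%, b = 10%: 1 - 0.5/1.1 = 54.5%, a shift of 4.5 points.
- R = 50%, b = 20%: 1 - 0.5/1.2 = 58.3%, a shift of 8.3 points.
- R = 70%, b = 10% and 20%: 1 - 0.3/1.1 = 72.7% and 1 - 0.3/1.2 = 75.0%, shifts of 2.7 and 5.0 points.
- R = 90%, b = 10% and 20%: 1 - 0.1/1.1 = 90.9% and 1 - 0.1/1.2 = 91.7%, shifts of 0.9 and 1.7 points.
- R = 100% (seizure-free): no shift for any b.

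These are shifts for a single patient. The effect on an arm mean is smaller, to the extent that patients in that arm become seizure-free.

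**The case against.** The best reply is that the article already dates the baseline that matters. General study design puts seizure status at about day -10, and screening needs a monthly frequency at Enrollment. None of the rows marked at day -7 enters the primary formula. The Allocation heading at day -7 suggests that the randomisation mark is simply misplaced. The text says patients and clinicians know the arm before surgery, not from day -10. Fig. 1, the study timeline, could not be read for this check and may settle the order. On blinding, *clinicians* may mean treating clinicians only, and the article does make a blinding statement.

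Much of this stands, and it rules out several stronger readings:

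- **The primary denominator is collected after randomisation.** A reader might infer this from Table 1, but the table gives the count no row and the text dates it to about day -10. It is possible, not stated.
- **Patients who decline surgery early have no baseline and drop out of the intention-to-treat set.** This would need the count to be taken only at day -7. The article does not say so, and Statistical analysis commits the primary outcome to intention-to-treat.
- **Outcomes are scored by unblinded assessors.** The text conflicts with itself. What can be said is that blinding to the main comparison is not secured.
- **The illustrated shift uses up much of the 10% noninferiority limit.** Sample size does not tie that limit to the mean remission rate; it speaks of effective rates and impairment rates. The two may be on different scales.

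The reply does not remove the contradiction between text and table, the missing row, the unstated order, or the limited scope of the blinding statement.

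**Conclusion.** The point holds as a failure to secure two safeguards, not as a demonstrated bias. First, Table 1 contradicts General study design on when baseline is taken, marks randomisation before the listed measures, and omits the primary-outcome denominator. With open allocation, baseline before knowledge of the arm is not assured. Second, Randomization and blinding and Data management cannot both be followed as evidence of blinding to lesioning versus resection.

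The size cannot be derived from the article. The shift of 4.5-8.3 points per patient assumes a true 50% reduction and 10-20% over-recording in one arm only. It shrinks as true remission rises and is zero for seizure-free patients. The correction is worth making because it is cheap and because neither weakness can be repaired once data are collected.

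**What to change.** - **Table 1:** put all baseline rows at the Enrollment visit (about day -10, matching General study design). Add a baseline seizure-frequency row there. Move randomisation to the Allocation column (day -7).
- **Randomization and blinding:** state that the envelope is opened only after baseline seizure frequency and the other baseline data have been entered in the eCRF and locked.
- **Blinding:** reconcile this section with Data management. State whether the outcome assessors are separate from the two evaluating clinicians, and what each is told. Where existing staff allow, have outcomes scored by assessors not told lesioning versus resection. Otherwise, withdraw the blinded-assessor claim for the main comparison.

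The cost is wording, a table correction and a small scheduling burden. The article does not describe staffing at each centre, so whether blinded assessors are available is for the sponsor to establish. If patients have already been enrolled under the current schedule, record for each whether baseline preceded randomisation.
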